### Trial design {8}

The 2-year study is conducted in a stepped wedge cluster randomized design [13]. Our clustered unit of analysis is a district, or *Kecamatan*, in Indonesia. Because we have two interventions, we are running two concurrent trials. Each intervention will involve 6 districts, for 12 districts involved total. Each district typically has one or two *Puskesmas* (*Pusat Kesehatan Masyarakat*) or community health clinics—the location of most vaccinations. Each district also is composed of several villages.

Our study location is Banda Aceh, the provincial capital of Aceh, and Aceh Besar, the surrounding suburban area. There are a total of 41 districts in Banda Aceh and Aceh Besar. We randomly sampled 18 of these. We subsequently performed a cluster analysis, where we clustered these 18 districts into 2 groups based on the following district-level characteristics: (a) population density; (b) *Puskesmas* building conditions—variables indicating the condition of *Puskesmas* buildings, such as good, lightly damaged, moderately damaged, and heavily damaged; (c) healthcare personnel—number of general practitioners, midwives, and community health workers in each district; (d) auxiliary *Puskesmas* conditions including good, lightly damaged, moderately damaged, and heavily damaged; (e) educational institutions—number of *Poskestren* (Islamic boarding schools); (f) healthcare facilities—number of beds and maternity care beds available; and (g) internet network availability—status of internet networks, including good, not smooth, and none.

The first group had 12 districts, and the second six districts. For the first 12 districts, we additionally removed six districts whose population center was close to the population center of another district to avoid spillovers. In this way, we ended with six districts in each group. We then randomly assigned the two groups to either the MVC strategy or the religious conference strategy. Thus, the six districts from the first group were assigned to the MVC strategy, and the six districts in the second group were assigned to the religious conference strategy (Table 1). For each group of 6, 3 districts were from Banda Aceh, and 3 from Aceh Besar. Within each group, we then randomized three districts to begin the intervention in year 1 and three in year 2 using a computer-generated allocation. District authorities were informed only after randomization. Although the strategies were implemented simultaneously, analytically, these are treated as two separate trials. The stepped wedge design and the district schedule for the two interventions are depicted in Fig. 1 and Table 1.

**Table 1 Tab1:** Sites of the two interventions, TABRIE, Aceh, Indonesia, 2023–2025

Strategy	Year(s) of intervention (randomized)	Location	District
Mobile vaccine clinic (MVC)	1 and 2	Banda Aceh	Baiturrahman
MVC	1 and 2	Banda Aceh	Jaya Baru
MVC	1 and 2	Aceh Besar	Mesjid Raya
MVC	2	Banda Aceh	Kuta Raja
MVC	2	Aceh Besar	Peukan Bada
MVC	2	Aceh Besar	Krueng Barona Jaya
Religious conference	1 and 2	Aceh Besar	Kuta Malaka
Religious conference	1 and 2	Aceh Besar	Darussalam
Religious conference	1 and 2	Banda Aceh	Meuraxa
Religious conference	2	Banda Aceh	Kuta Alam
Religious conference	2	Banda Aceh	Lueng Bata
Religious conference	2	Aceh Besar	Montasik

Year of intervention start was randomized within each intervention arm (3 districts began in year 1 and 3 in year 2)

**Fig. 1 Fig1:**
[figure not shown]
Modified stepped wedge design of the TABRIE study. 1.Notes: We are running two concurrent interventions - Mobile Vaccine Clinic (MVC) and Religious Conference. Each intervention involves 6 districts. 2023 was the baseline year with no intervention assignment

## Methods: participants, interventions, and outcomes

### Study setting {9}

Aceh is a religiously conservative region in Indonesia and has been granted more autonomy by the national government. From a recent paper we wrote using 2017 data, pediatric measles vaccination coverage was 54% in Aceh, the lowest of any province in Indonesia, indicating a need for more innovative vaccine delivery models [14]. A recent study of social media use in Indonesia found that vaccine misinformation clustered around concerns about halal certification, industrial conspiracies, and concerns about side effects [15].

### Eligibility criteria {10}

To be eligible for the study; the participant should: (a) adults 18 or older; (b) proficient in Bahasa Indonesia; (c) plan to live in neighborhood for next year; and (d) parent of child <5. Eligibility criteria apply to the surveyed household population (children 1–5 years of age and their parents) which is the basis of the primary outcome.

### Who will take informed consent? {26a}

Study staff will be trained in ethical considerations and study procedures and will be responsible for obtaining informed consent. For participant recruitment, study staff will randomly select households from the birth registry at the Puskesmas that include children meeting the study criteria. The selected households will then be contacted by telephone, and if they agree to participate, the interview will be conducted either in their homes or at designated locations. Study staff will explain the contents of the form, ensuring participants understand the purpose of the study, their rights, and the voluntary nature of participation. Before starting the questionnaire, staff will ask, “Is this a good place and time to talk?” If privacy concerns arise, the interviewer will either identify a more private location or arrange to return later to complete the interview.

All informed consent procedures will be conducted by the trained study staff. We will document written informed consent. Participants will receive a copy of the informed consent form for their records.

### Additional consent provisions for collection and use of participant data and biological specimens {26b}

N/A.

## Interventions

### Explanation for the choice of comparators {6b}

The control groups receive standard outreach from healthcare workers, i.e., *Puskesmas* staff conduct regularly scheduled outreach activities in each of the villages in the control districts. This is the comparator of choice since the aim of the study is to assess if the two strategies lead to increased vaccination coverage compared to current outreach activities.

### Intervention description {11a}

The study comprises two distinct interventions. The first intervention is a religious conference that will bring together subdistrict-level imams, other religious leaders, and a variety of community health workers, including those not traditionally trained to administer vaccines. The conference will feature both joint sessions with all participants and breakout sessions tailored by profession. The topics covered during the conference will be developed collaboratively with the religious leaders, with a primary focus on the importance of infant health and vaccination. After the religious conference, we will also follow up with some religious leaders at later points in the year.

The second intervention is a mobile vaccine clinic (MVC), where a community health worker will travel to different locations within the test districts. These locations will be chosen in collaboration with the local health department and based on the research team’s understanding of the area. Targeted sites will include spaces frequented by families with young children, such as schools, mosques, and sports fields. The purpose of the mobile clinic is not only to deliver vaccines but also to personalize vaccine delivery by introducing a human connection—represented by the community health worker—outside of a clinical setting. The community health worker will be equipped to administer vaccines and address any questions or concerns individuals may have.

### Relevant concomitant care permitted or prohibited during the trial {11d}

N/A.

### Provisions for post-trial care {30}

N/A.

### Outcomes {12}

The primary outcome is full vaccination, which is ascertained through records from vaccination cards or clinic records. Secondary outcomes are also listed in Table 2, along with the original measure in the survey instrument, and how it is re-coded (as applicable).

**Table 2 Tab2:** Primary and secondary outcome measures

**#**	**Description**	**Measurement**	**Recode**
Primary outcome			
1	Full vaccination	Records from vaccination cards or clinic records 6 months since the start of the intervention: 1 dose of BCG; 3 doses of DTP; 3 doses of polio vaccine; 1 dose of measles-containing vaccine	
Secondary outcomes			
2a	DTP dose 1 vaccination	Records from vaccination cards or clinic records	
2b	Measles dose 1 vaccination	Records from vaccination cards or clinic records	
2c	Vaccine hesitancy	Overall, how hesitant about childhood shots would you consider yourself to be ● Not at all hesitant (1) ● Not that hesitant (2) ● Somewhat hesitant (3) ● Very hesitant (4) ● Unsure (5) ● Refused (6)	Dichotomized (3 + 4 is hesitant, other responses and missing responses count as non-hesitant)
2d	Social norms of vaccination	Do you think most parents you know vaccinate their children? ● Yes (1) ● No (2) ● Don’t know (3)	Dichotomized (1 is yes, other responses and missing responses count as no)
2e	Trust in community health workers	How much would you trust your child being vaccinated by a community health worker in a mobile vaccine clinic? ● Strongly distrust (1) ● Distrust (2) ● Neither trust or distrust (3) ● Trust (4) ● Strongly trust (5)	Dichotomized (4 + 5 is trust, other responses and missing responses count as do not trust)
2f	Distance barrier	What barriers have you encountered in getting your children vaccinated? (Select all that apply) ● [Other options provided] ● The distance from my residence to the vaccination site is too far (6)	Dichotomized (selecting 6 is yes, other responses and missing responses count as no)
2g	Vaccination norms from religious leaders	Do you think your religious leaders want you to vaccinate your children? ● Yes (1) ● No (2) ● Don’t know (3)	Dichotomized (1 is yes, other responses and missing responses count as no)
2h	Information from religious leaders	How and where did you hear information about the vaccination program for your children? (Select all that apply) ● [Other options provided] ● From religious leaders (6)	Dichotomized (selecting 6 is yes, other responses and missing responses count as no)

### Participant timeline {13}

Cross-sectional surveys will be conducted September of each year from 2023 to 2025. Baseline year is 2023, year 1 of the interventions is 2024, and year 2 is 2025. In each year, a religious conference will be held in January. We expect that participants will disseminate vaccine promotions to their communities after this date. We will also follow up with participants from the conference in March and June. For the MVCs, community health workers will conduct outreach events in two rounds. Round 1 will be in January and February, and round 2 will be in May and June (Fig. 2).

**Fig. 2 Fig2:**
[figure not shown]
Timeline of intervention strategies in a stepped wedge cluster randomized control trial, TABRIE, Aceh, Indonesia, 2023–2025

### Sample size {14}

For this cluster randomized control trial, we specified a stepped wedge design with baseline measures and a cross-sectional sampling structure. The primary outcome is the net difference between arms in repeated cross-sectional samples. We used the following parameters for sample size calculation: (a) type I error rate: 0.05; (b) power: 0.80; (c) expected vaccination proportion in controls: 49.5% (based on the 2022 survey); and (d) intraclass correlation coefficient (ICC): 0.0816 (based on the 2022 survey).

To detect a 13 percentage point increase in vaccination coverage (62.5% in the intervention arm vs. 49.5% in the control arm), we determined that 100 individuals per cluster are required. With a stepped wedge design involving three clusters in the first year and three in the second year, this sample size provides adequate power to detect the specified effect size. The sample size calculation assumed an exchangeable (time-invariant) intracluster correlation; no temporal decay was assumed.

### Recruitment {15}

We are conducting a series of cross-sectional surveys as part of this trial. For each district, we will obtain a household listing with a child aged 1–5 years from the *Puskesmas* catchment area and will randomly select the households. Enumerators will contact the selected households by telephone, and if they agree to participate, the interview will be conducted either in their homes or at designated locations. If a household refuses or is ineligible, the next randomly drawn household will be contacted and approached. Survey enumerators do not disclose intervention allocation or timing to sampled households. Communities might be informed of the upcoming MVC or religious conferences through the routine mobilization processes that are part of the individual interventions.

## Assignment of interventions: allocation

### Sequence generation {16a}

N/A.

### Concealment mechanism {16b}

N/A.

### Implementation {16c}

In this stepped wedge design, participants’ intervention is determined by where they live. Participants are enrolled into the study by a team of trained enumerators.

## Assignment of interventions: blinding

### Who will be blinded {17a}

N/A.

### Procedure for unblinding if needed {17b}

N/A.

## Data collection and management

### Plans for assessment and collection of outcomes {18a}

Protocol and data collection instruments can be found here: 10.6084/m9.figshare.25991875.

### Plans to promote participant retention and complete follow-up {18b}

N/A.

### Data management {19}

As data is collected and entered into a secure database, the study team will regularly tabulate results for the primary and secondary objectives to monitor data quality issues. Although we do not anticipate adverse events being observable in the data, regular quality checks will ensure completeness, accuracy, and consistency.

Compliance with regulatory documentation and study data integrity will be maintained through an internal quality assurance process implemented by the study team.

Confidentiality will be safeguarded throughout the trial. Informed consent forms, enrollment forms, and questionnaires will be stored in separate secure locations. After the questionnaires are input into an electronic database, the physical copies will be destroyed to further protect participant information. Informed consent forms will be retained for the duration specified by the institutional review boards (IRBs).

The data will initially be stored on a secure, HIPAA-compliant online platform—such as Dropbox—that is supported by the University of Michigan. While data collection is ongoing and some personally identifiable information may temporarily reside in the database, access to the folder will be password-protected and restricted to authorized study team members only.

### Confidentiality {27}

Reproducibility and replicability are critical to advancing scientific knowledge and ensuring transparency in research. To this end, we plan to upload the final dataset, along with detailed statistical analysis code, to a public repository such as Figshare. Prior to publication, all personally identifiable information will be removed from the dataset to protect participant confidentiality. Additionally, geographic locations will be anonymized by replacing specific identifiers with coded numbers, ensuring that individuals cannot be located or identified.

### Plans for collection, laboratory evaluation, and storage of biological specimens for genetic or molecular analysis in this trial/future use {33}

Not applicable.

## Statistical methods

### Statistical methods for primary and secondary outcomes {20a}

We will report descriptive statistics, including demographic characteristics by cluster and by intervention arm.

The primary outcome is a binary variable: full vaccination (Table 2). For the main analyses, we will include one randomly selected child aged 1–5 years from each family. All models will adjust for the following pre-specified covariates: (a) respondent characteristics such as age, gender, education (less than high school, high school, more than high school), and ethnicity (Acehnese vs. non-Acehnese) and (b) child characteristics such as age (1-, 2-, 3-, 4-year-old), gender, and birth order.

### Primary outcome analysis: mixed-effects logistic regression

To evaluate the primary outcome, we will use a generalized linear mixed model (GLMM) model with a logit link, including period-fixed effects and a cluster-level random intercept to account for intracluster correlation. The outcome of full vaccination will be specified as the dependent variable, with experimental condition as a dummy variable to estimate the treatment effect.

We will include data from all years and all clusters, adjusting for time and covariates

$$\begin{aligned} logit(P({Y}_{ijk}=1))={\beta}_{0} &\,+{\beta}_{1}\cdot Treatment_{jk}+\gamma_{1}1\{k=1\}\\ &\,+\gamma_{2}1\{k=2\} + X_{ijk}^T\beta_2+{u}_{j} \end{aligned}$$

$${\beta }_{1}$$: treatment effect (log-odds)

$${\gamma }_{k}$$: time trends independent of the treatment, where $$\textrm{k} \in \{1,2\}$$

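### The primary model gives the second-year effect negative weight, so its single treatment coefficient is the treatment effect only if that effect is the same in both years of exposure, and no planned model can check this

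*Protocol article*

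**What the plan says.** The section on the primary outcome analysis gives the model as an equation: period fixed effects, a district random intercept, covariates, and one treatment indicator with one coefficient beta1, "with experimental condition as a dummy variable to estimate the treatment effect". On the data used it says: "We will include data from all years and all clusters, adjusting for time and covariates".

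The note to Table 1 states: "Year of intervention start was randomized within each intervention arm (3 districts began in year 1 and 3 in year 2". The table lists early-start districts as receiving the intervention in years 1 and 2, and late-start districts in year 2 only. Delivery is repeated; for the religious arm, the participant timeline says: "In each year, a religious conference will be held in January". The mobile clinics run two rounds of outreach. Table 2 defines the primary outcome as a completed multi-dose record.

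The secondary analysis section allows for an effect that varies over time, through interactions of treatment with calendar period. The interim section gives a model with a single Year 1 period term and calls its coefficient a preliminary treatment effect.

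**The concern.** All six districts of each trial are treated at the September 2025 survey. With one treatment coefficient, the model takes the early-minus-late difference at that survey to be pure district difference and uses it to correct the Year 1 contrast. That is valid only if a second year of exposure adds nothing to the first and loses nothing from it. If it does either, part of the real effect enters the correction with the wrong sign. beta1 is then not an average of the first- and second-year effects and can lie outside both. This bears on the only primary estimate in each of the two concurrent trials, and the final analysis contains no model that would show it.

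**Working it through.** **Inputs.** From the sample size section: "type I error rate: 0.05" (sidedness not stated, two-sided assumed), power 0.80, "To detect a 13 percentage point increase in vaccination coverage (62.5% in the intervention arm vs. 49.5% in the control arm", ICC 0.0816 with exchangeable correlation, and 100 individuals per cluster, read here as per district per survey. From the trial design section: six districts per trial, three per sequence, and two trials analysed separately. Treatment patterns over the three surveys are (0,1,1) for early-start and (0,0,1) for late-start districts.

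**The plan's own figure.** I used the Hussey-Hughes variance for a cross-sectional stepped wedge.
- Total variance, averaged over arms: (0.495*0.505 + 0.625*0.375)/2 = 0.2422.
- Between-district variance: 0.0816*0.2422 = 0.01976.
- Variance of a district-survey mean within district: 0.9184*0.2422/100 = 0.002224.
- Normal-theory power for 13 points is 0.794 (0.787 with the pooled variance), so the stated 0.80 is reproduced.

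**Weights.** Let a = 100*0.0816/0.9184 = 8.885. The estimator of beta1 is the Year 1 early-minus-late difference, minus w times the baseline difference, minus w times the Year 2 difference, where w = a/(1 + 2a) = 8.885/18.770 = 0.473.

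SE(beta1) = sqrt{(2/3)*[0.002224*(1 + 2*0.473^2) + 0.01976*(1 - 2*0.473)^2]} = 0.0467.

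**Expectation when the effect depends on exposure.** True effects are (0, d1, d2) in early-start and (0, 0, d1) in late-start districts. The early-minus-late differences are therefore 0, d1 and d2 - d1, so

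E[beta1] = d1 - 0.473*(d2 - d1) = 1.473*d1 - 0.473*d2.

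**Size.** The ratio d2/d1 is an assumption; d1 = 13 points.

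| d2/d1 | E[beta1], points | Normal-theory power |
|---|---|---|
| 0.5 | 16.1 | 0.93 |
| 1 | 13.0 | 0.79 |
| 1.25 | 11.5 | 0.69 |
| 1.5 | 9.9 | 0.56 |
| 2 | 6.8 | 0.31 |

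The result depends little on the ICC: the weight on d2 is -0.33 at ICC 0.01, -0.46 at 0.05 and -0.49 at 0.20.

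**Logistic scale.** The planned model is logistic, so the formula is an approximation. Simulated fits of the logistic mixed model without covariates (true first-year log odds ratio 0.531, 150 runs per scenario) gave mean beta1/d1 of 1.05, 0.81 and 0.60 at ratios 1, 1.5 and 2, with Monte Carlo error about 0.03. Direction and approximate size agree with the linear result (1.00, 0.76, 0.53).

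**Can the planned interaction model detect it?** No, for two reasons. It assigns one Year 2 effect to all districts, whatever their exposure. And in Year 2 treatment equals 1 in every district, so Treatment x 1{k=2} is the same column as 1{k=2}. The five fixed-effect columns have rank 4, and beta12 cannot be separated from gamma2.

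**Exposure-time model.** Use separate indicators for the first and second year of exposure, with coefficients delta1 and delta2.
- delta1 gives Year 2 zero weight. It is the Year 1 difference minus 0.899 times the baseline difference, where 0.899 = 0.01976/(0.01976 + 0.002224).
- SE(delta1) = sqrt{(2/3)*0.02199*(1 - 0.899^2)} = 0.0531. Power for 13 points is about 0.69.
- Equal power with beta1 requires 1 - 0.473*(d2/d1 - 1) = 0.0467/0.0531, that is, growth of about 25%.

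**The case against.** The strongest reply is that everything turns on d2/d1, which the documents do not give. If the effect is constant, beta1 is unbiased and more precise than delta1. If there is no effect in either year, beta1 is centred on zero, so this mechanism produces no false positive. The single-indicator model also matches the sample size calculation. All of this stands.

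A reader might go further and infer that growth is the expected case, because vaccination status accumulates, and hence that the primary result is biased toward zero. The documents do not support that. The surveys are repeated cross-sections, and the covariate list has child ages 1 to 4, so roughly one birth cohort in four leaves the sampled range each year. After a first-year catch-up, fewer unvaccinated children may remain to be reached. In the mobile clinic trial, the Discussion reports that some health workers in Jaya Baru, one of its three early-start districts, refused to cooperate in year 2. That points toward a weaker second-year effect, which would bias beta1 upward. The direction is therefore open. The planned leave-one-out analysis for that district addresses the disruption, not the constant-effect assumption.

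It is also fair to say that a clean first-year contrast is already written down: the interim model, read as fitted to baseline and Year 1, estimates it. But it is labelled preliminary and has no stated place in the final analysis. The six-month wording in Table 2 does not equalise exposure either, since the surveys are held each September and early-start districts are treated in both years.

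Finally, changing the primary model is not free. It costs about 10 points of power under a constant effect. The article also appeared in November 2025, after the planned final survey and with an interim Year 1 estimate foreseen, so a change could look informed by results.

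**Conclusion.** The point holds in a limited form. The negative weight on the second-year effect is algebra for this two-sequence, three-survey layout, at -0.473 with the plan's own ICC and cluster size. How far beta1 departs from the first-year effect, and in which direction, depends on d2/d1, which has to be assumed: about 12% below at 25% growth, 24% below at 50%, 47% below at doubling, and 24% above if the effect halves. These figures assume the linear scale, 100 children per district per survey and exchangeable correlation. The documents do not establish that the primary result is biased toward zero, or that the primary model must be replaced. They do establish that beta1 rests on an unstated constant-effect assumption, and that the model offered to test variation over time cannot test it and contains a term that cannot be estimated.

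**What to change.** Replace the treatment-by-calendar-period model with an exposure-time model: the same period effects, random intercept and covariates, with separate indicators for the first and second year of exposure. Report delta1 beside beta1 in the final analysis. State that beta1 can be read as the treatment effect only if the effect is constant over exposure. State also that delta2 relies on late-start districts having the same first-year effect as early-start districts.

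This costs nothing in design or data: the number of fixed-effect terms stays the same and the unidentified one goes. delta2 will be imprecise. It is the sum of the Year 1 and Year 2 differences minus 1.798 times the baseline difference, so its SE is sqrt{(2/3)*[0.002224*(2 + 1.798^2) + 0.01976*(2 - 1.798)^2]}, about 0.091. It should be presented with its interval and not used as a pass-or-fail test of constancy.

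The sponsor may instead make delta1 the primary estimand. In that case the stated power for 13 points should be restated as about 69% rather than 80%, and the date of the change given relative to any look at the Year 1 or Year 2 results.
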